**Figure 3. F3:**
[figure not shown]
Web page created for the IM-OA23 project. The image shows the project name accompanied by the following phrase: “Innovating in breast cancer care to improve quality of life. Learn more.”

The videos will be structured as follows: first, a black screen will appear, and a female voice will provide the instructions for performing the therapies. Next, the video will display the movement chosen for the AO therapy. The black screen will then appear again, and 2 acoustic signals will play, indicating the start and end of the MI task. During the MI phase, the participants will be instructed to perform kinesthetic MI from a first-person perspective, imagining themselves executing the observed movement and focusing on the sensations associated with the action. The same process will be subsequently repeated with the next selected movement. The videos will last between 6 and 10 minutes. After viewing the videos and performing the MI and AO therapies, the participants will actively perform the exercises displayed previously in the screens.

### Control Condition

The CG will perform the same movement exercises as the IG but without the addition of MI or AO therapies. All the participants will perform mobility exercises of the upper limb involving flexion, extension, abduction, adduction, internal rotation, and external rotation for approximately 20 minutes 3 times a day 3 times a week for the duration of the intervention (6 weeks).

Once participants consent and are allocated to the CG, sociodemographic and clinical data will be collected, and the remaining variables will be measured (T0). Finally, participants will receive detailed instructions on the exercises, including the number of series and repetitions per series, along with a diary to record exercise frequency throughout the established 6 weeks. Follow-up assessments will be scheduled at 6 weeks (T1) and 3 months (T2).

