### Randomization, Allocation, and Blinding

The participants in the study will be randomly assigned to 1 of 2 groups: the IG (MI+AO+mobility exercises) or the CG (mobility exercises alone). All the participants will perform mobility exercises of the upper limb involving flexion, extension, abduction, adduction, internal rotation, and external rotation for approximately 20 minutes between 1 and 3 times a day 3 times a week for the duration of the intervention (6 weeks).

The randomization process will be carried out using the Research Randomizer tool and an allocation ratio of 1:1 with the aim of guaranteeing impartiality and validity in the study and ensuring a balanced distribution, simple randomization, and a reduction in biases while preserving the integrity and reliability of the results. The randomization list will be created by a member of the research team without contact with participants or access to personal or clinical information.

This is a single-blind study, as neither participants nor the researchers delivering the intervention can be blinded. Blinding will be maintained for the researchers responsible for collecting outcome data, administering evaluation instruments, and performing the statistical analyses.

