### Intervention: the IM-OA23 Program

The study intervention is part of the IM-OA23 program, a structured initiative designed to integrate MI and AO into rehabilitation strategies. Support for the intervention will be presented in video format and will be accompanied by instructions for performing the MI and OA therapies as well as the additional mobility exercises, with a video prepared to help participants perform the therapies.

The intervention will last 6 weeks, during which the content of the program will be progressively modified. During the first 2 weeks, the following anatomical movements will be visualized and imagined, with an approximate duration of 20 seconds per movement: (1) arm flexion from 0 to 180°, (2) arm extension from 0 to −10°, (3) arm abduction from 0 to 180°, (4) arm adduction from 0 to 45°, (5) internal arm rotation from 0 to 45° with the elbow flexed at 90°, (6) external arm rotation from 0 to 45° with the elbow flexed at 90°, and (7) forward and backward arm circumductions (Figures1  2 [38]). In the third and fourth weeks, the participants will progress to performing the anatomical movements described above with a small weight, for example, a 1-kg dumbbell. The videos will depict a woman dressed in black in the frontal and lateral planes performing the described anatomical movements. In the final 2 weeks (fifth and sixth), the content will focus on ADLs through the following tasks: (1) reaching for a jar, (2) raising and lowering blinds, (3) drawing a curtain, (4) changing a light bulb, (5) stirring a pot, (6) scratching one’s back, (7) stretching, (8) putting on and taking off a coat, (9) hugging someone, (10) cleaning a window pane, (11) turning the steering wheel of a car, and (12) throwing a ball.

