**Figure 2. F2:**
[figure not shown]
Audiovisual resources developed. The images illustrate the exercises assigned for weeks 1 and 2.

For each of the movements and ADLs, AO will be performed first, followed by MI. After the completion of the MI and AO blocks, the participants will also carry out mobility exercises involving repeating the movements they saw in the videos.

As indicated, all the participants will perform upper-extremity mobility exercises involving flexion, extension, abduction, adduction, internal rotation, and external rotation. They will perform the mobility exercises for approximately 20 minutes per session between 1 and 3 times per day on 3 different days per week throughout the 6-week intervention period. The minimum dose will be 1 time per day on 3 different days per week, and the maximum dose will be 3 times per week on 3 different days per week.

Each participant will be instructed on how to access the audiovisual resources developed specifically for this study and hosted on a dedicated website (Figure 3). They will also receive an information sheet describing the exercises and a field diary to record the frequency of intervention practice during the established weeks. At the end of the explanation, the participant will be scheduled for data collection at 6 weeks (T1) and 3 months (T2).

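### The exercise prescription contradicts itself on frequency and content, so the document does not establish that the trial compares MI+AO added to identical exercise

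*Protocol article*

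**What the plan says.** **The contrast.** The abstract and the Randomization, Allocation, and Blinding section define the groups as MI+AO plus mobility exercises versus mobility exercises alone.

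**Frequency.** Three places set it, each time for all participants:
- Randomization, Allocation, and Blinding: "approximately 20 minutes between 1 and 3 times a day 3 times a week for the duration of the intervention (6 weeks".
- Intervention: the IM-OA23 Program (text after Figure 2): "approximately 20 minutes per session between 1 and 3 times per day on 3 different days per week". The same paragraph then gives a minimum of one session a day on 3 days a week, and adds that "the maximum dose will be 3 times per week on 3 different days per week".
- Control Condition: "approximately 20 minutes 3 times a day 3 times a week for the duration of the intervention (6 weeks".

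**Content.** The Intervention section describes a program that changes every 2 weeks. Weeks 1 and 2 cover seven items: six shoulder movements plus circumductions. In weeks 3 and 4 "the participants will progress to performing the anatomical movements described above with a small weight, for example, a 1-kg dumbbell". Weeks 5 and 6 turn to 12 daily-living tasks. After the MI and AO blocks, "the participants will also carry out mobility exercises involving repeating the movements they saw in the videos"; the description of the videos after Figure 3 says the same in other words. The Control Condition section states: "The CG will perform the same movement exercises as the IG but without the addition of MI or AO therapies". Its next sentence lists six movements, with no circumduction, weight, daily-living task or weekly progression.

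**The concern.** The control group exists to hold physical exercise constant, so that a difference between groups can be read as the effect of MI+AO. That reading needs one exercise prescription with the same amount and content in both groups, and the document gives no single one.

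If the conflicting statements were applied differently by group, the bias could run either way. More sessions among controls could mask a benefit of MI+AO. Weighted movements and task practice in the intervention group only could produce a benefit that is then credited to MI+AO. Physical exercise could plausibly affect pain (the primary outcome, with T1 as the primary time point) and shoulder range. Participants work from written instructions, with web videos in the intervention group, and record practice in a diary. What they were told is therefore much of the treatment, and the Study Limitations section already accepts that adherence rests on self-report.

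**Working it through.** **Inputs.** About 20 minutes per session and 6 weeks (all three sections); 1 to 3 sessions a day on 3 days a week (Randomization and Intervention sections); 3 sessions a day, 3 times a week (Control Condition); 3 times per week as the stated maximum (Intervention section). The document gives no total dose to reproduce.

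**Formula.** Sessions = sessions per day × days per week × 6. Hours = sessions × 20 / 60.

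| Statement | Sessions per week | Sessions in 6 weeks | Hours |
|---|---|---|---|
| Low end of range, and stated minimum | 1 × 3 = 3 | 18 | 6 |
| High end of range | 3 × 3 = 9 | 54 | 18 |
| Stated maximum, read literally | 3 | 18 | 6 |
| Control Condition | 3 × 3 = 9 | 54 | 18 |

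Two conflicts follow. The Control Condition figure is fixed at 54 sessions where the other sections allow 18 to 54. The literal maximum equals the minimum, and so contradicts the range given just before it.

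**Between-group range.** If the Control Condition figure was applied to controls and the range to the intervention group, the ratio of control to intervention sessions runs from 54/54 = 1 to 54/18 = 3. If any one statement was applied to both groups, the prescribed ratio is 1.

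**Content, side by side.**

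| Weeks | Active content from the videos (intervention group) | Listed under Control Condition |
|---|---|---|
| 1–2 | Six movements plus circumductions | Six movements |
| 3–4 | The same, with a small weight | Six movements, no weight mentioned |
| 5–6 | 12 daily-living tasks | Six movements |

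The video content departs from the six-movement list in 4 of the 6 weeks, or in all 6 if circumductions count. No section explicitly gives controls the circumductions, the weight or the tasks.

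**Sample size.** This is unaffected. With SD 2.61, difference 1.5, 80% power and alpha 0.05 (taken as two-sided), n = 2 × (1.96 + 0.84)² × 2.61² / 1.5² gives 48 per group after rounding up. Then 48 / 0.9 rounds up to 54 per group, or 108 in total, as stated.

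**The case against.** A reader might infer that controls were prescribed up to three times as much exercise as the intervention group. The text does not support that. No section splits frequency by group, and the sentence under Control Condition also takes all participants as its subject. It nearly repeats the sentence in the Randomization section without the range, so a drafting slip is a plausible explanation. The odd maximum may be another slip, and since it is worded for everyone it does not itself separate the groups.

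A reader might also infer that the control content is known to differ. That is not shown either. The same six-movement list is given for all participants in the Intervention section, although the intervention group plainly does more than the list. The list may therefore be a summary, and the statement that controls do the same exercises may be meant to include the weight and the tasks. The detailed instructions given to controls are not shown.

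Finally, randomization keeps the comparison of the program with the control prescription valid whatever the exercise content, and the stated aim is to evaluate a program.

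All of this stands, and it limits the conclusion. It does not remove the point: these are conflicting statements, not detail that an article leaves to a fuller document, and they concern the element that is supposed to be equal in the two groups.

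**Conclusion.** The concern holds as an internal contradiction in the prescription that defines the trial's contrast. The document gives two incompatible frequencies (18 to 54 sessions, or a fixed 54), a maximum that literally equals the minimum, and a claim of identical exercises that its own lists do not bear out for 4 to 6 of the 6 weeks. As written, it does not establish that the comparison is MI+AO added to identical exercise.

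It does not prove the opposite. The 3-fold gap is an upper bound that assumes the Control Condition figure was used for controls and the low end of the range for the intervention group. It also does not follow that the result cannot be attributed to MI+AO; that depends on what the women were told and did. The documents give no figure for how a difference in active exercise would move pain at T1, so the bias cannot be sized.

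**What to change.** 1. Reconcile the Randomization, Intervention and Control Condition sections into one statement of frequency and weekly active content, and say explicitly whether it is identical in both groups. The values are for the sponsor's clinical team.
2. Check the information sheets and exercise instructions for what the roughly 80 women already recruited were told, by group, and record any change for those still to enter.
3. Report completed sessions by group from the diaries planned for both groups. Confirm that the intervention group's diary lets active exercise be counted separately from MI+AO practice.
4. If the groups differed in amount or content of active exercise, word the conclusion as the IM-OA23 program versus the control exercise prescription, not as the effect of MI+AO alone.

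The cost is protocol wording, a check of participant materials and a descriptive table. It needs no new data collection if the diaries separate the two activities, and no change to the sample size. Analysis had not started when the article was submitted, so this can still be settled before results are known.

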### Variables and Measurement Instruments

The independent variable will be the IM-OA23 program, which will combine MI and AO therapies. There will be 6 dependent variables.

Pain is the primary outcome variable. It will be evaluated using the NRS, one of the most widely recommended and commonly used tools for assessing pain intensity in a simple, quick, and reliable way. It is an objective scale that quantifies the intensity of pain, similar to the visual analog scale. The NRS is an 11-point scale presented as a horizontal line, with 0 indicating “no pain” and 10 indicating “the worst pain imaginable” or “the worst pain that can exist.” Participants will be asked to report their average pain or pain experienced in the previous 24 hours [39].

Joint range, the degree of movement of the shoulder joint, will be measured using a goniometer. Flexion, abduction, and internal and external rotation will be measured using previously established reference points [40].

Muscular strength, the grip strength of the affected limb, will be measured using a dynamometer (Jamar). The measurement will be made with the participant in a sitting position with the elbow at 90° flexion, the shoulder close to the torso, and a neutral wrist position. The maximum achievable force will be recorded from the best value of 3 attempts [41,42].

Fear of movement will be measured with the Tampa Scale of Kinesiophobia, adapted to Spanish. The scale consists of 11 items rated on a 4-point Likert scale (1-4), yielding a total score from 11 to 44, with higher scores indicating greater fear of movement [43,44].

The diameter of the affected limb will be measured using anthropometric tape with a precision of 1 mm. The measurement will be made at the midpoint between the acromion and the olecranon, leaving the tape perpendicular to the extremity without compressing the area. The midpoint will be located at 90° elbow flexion, and subsequently, the measurement will be obtained with the elbow in extension; the result will be recorded in centimeters [45].

Imagination capability will be assessed using the Movement Imagery Questionnaire–Revised, Second Edition, an 8-item instrument. The questionnaire requires 2 tasks: first, creating a drawing or a mental image of a movement and, second, attempting to feel the sensation of performing the movement without physically executing it. The difficulty of each item will be rated on a 7-point scale ranging from 1 (“very difficult to see/feel”) to 7 (“very easy to see/feel”). The total score is obtained by adding the scores of all the questions. Higher scores correspond to greater ease of imagination and perceived vividness [46].

### Data Collection

As previously described in the Setting section, participants will be enrolled through the dissemination of study information via various media, including the press, social networks, and SARAY. The study information will include a Google Forms questionnaire in which participants can express their interest in taking part and provide their contact information. All respondents to the questionnaire will be invited to an individual meeting with the research team, during which study information will be provided, questions will be addressed, and written informed consent will be obtained upon confirmation of participation. Subsequently, the planning of the intervention and data collection will be explained, and the assigned group will be indicated to each participant.

In both the IG and CG, outcomes will be assessed at 3 time points. The preintervention time point (T0) will coincide with the initial meeting and study inclusion, during which sociodemographic and clinical data will be collected, along with the other study variables. The postintervention time point will take place at 6 weeks (T1). Follow-up (T2) will subsequently be carried out 3 months after the end of the intervention to determine whether the effects have persisted over time (Figure 4). Pain will be considered the primary outcome, and the primary time point to evaluate the effectiveness will be T1. To collect the data, an electronic questionnaire will be designed with the help of the Microsoft Forms tool.

**Figure 4. F4:**
[figure not shown]
Timeline of the study. AO: action observation; BCLE-SEI-ES: Spanish version of the Breast Cancer and Lymphedema Symptom Experience Index; MI: motor imagery; MIQ-R: Movement Imagery Questionnaire–Revised; NPSI: Neuropathic Pain Symptom Inventory; NRS: numerical rating scale; TSK-11SV: Spanish version of the Tampa Scale of Kinesiophobia.

The IG will participate in the IM-OA23 program.

### Data Analysis

First, a descriptive analysis of all study variables will be performed. Continuous variables will be summarized using means and SDs (or medians and IQRs), and categorical variables will be summarized using frequencies and percentages.

The normality of outcome distributions will be assessed for each study group and time using the Kolmogorov-Smirnov test with Lilliefors correction. If normality assumptions are not satisfied, equivalent nonparametric approaches will be considered.

Baseline comparability between groups will be assessed using a 2-tailed Student *t* test (or Wilcoxon rank-sum test if normality is not met) for continuous variables and chi-square or Fisher exact tests for categorical variables.

Second, inferential analyses will be carried out following an intention-to-treat approach whereby all randomized participants will be included in the analyses focused on between-group comparisons (intervention vs control) based on pretest-posttest change scores. Missing data will be imputed and included in all analyses.

The primary analysis will consist of evaluating the effect of the intervention on pain at T0, T1, and T2 comparing changes between the IG and CG from baseline using a linear mixed-effects model.

For all outcome variables meeting normality assumptions, longitudinal trajectories will be evaluated using linear mixed-effects models with participant-specific random intercepts for within-subject correlation. The models will include fixed effects for group (control vs intervention), time (baseline, T1, and T2), and the group × time interaction. Standardized effect sizes (Cohen *d*) will be calculated from the adjusted between-group differences in change from baseline estimated by the mixed-effects models. Effect size will be interpreted as very small for values of less than 0.20, small for values of 0.20 to 0.49, moderate for values of 0.50 to 0.79, and large for values of 0.80 or more.

For variables not meeting normality assumptions, appropriate nonparametric methods will be considered. Between-group comparisons of change scores at each follow-up will be performed using the Wilcoxon rank-sum test.

In all cases, the significance level will be set at .05. The data will be analyzed using the SPSS program (version 27; IBM Corp).

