### Sample Size

To determine the sample size, we assumed a type I error of 0.05 and a type II error of 0.20 (80% power). The calculation was based on a minimum detectable difference of 1.5 points in pain intensity measured using the numerical rating scale (NRS). This minimum difference aligns with established minimal clinically important difference values for the NRS in breast cancer–related pain contexts, which range from 1.39 to 2.0 points [30-33].

An estimated SD of 2.61 was selected based on a conservative approach considering the variability reported in breast cancer populations using the NRS, where SDs range from 1.4 to 2.8 [34-37]. This conservative estimate ensures adequate statistical power even if data dispersion is greater than anticipated. Considering an estimated 10% dropout, the required sample size was 108 women, with 54 allocated to the control group (CG) and 54 allocated to the intervention group (IG). The power calculations were performed using the GRANMO online program (version 7.12; Programa de Registre Gironí del Cor).

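### The analysis section contradicts itself on whether the mixed model for pain depends on a normality test, one that 0–10 integer scores would seldom pass

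*Protocol article*

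**What the plan says.** All the analysis statements are in the protocol article, Data Analysis:

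- A pretest: "The normality of outcome distributions will be assessed for each study group and time using the Kolmogorov-Smirnov test with Lilliefors correction". With two groups and three time points this makes six tests per outcome. If normality fails, nonparametric equivalents are to be considered.
- The primary analysis: "The primary analysis will consist of evaluating the effect of the intervention on pain at T0, T1, and T2", by comparing change from baseline between groups in a linear mixed-effects model. No condition is attached.
- The general rule in the next paragraph: "For all outcome variables meeting normality assumptions, longitudinal trajectories will be evaluated using linear mixed-effects models with participant-specific random intercepts". Fixed effects are group, time and their interaction, and Cohen d comes from the model's between-group differences in change.
- The alternative: "For variables not meeting normality assumptions, appropriate nonparametric methods will be considered". The sentence after it is firmer and says that change scores will be compared at each follow-up by the Wilcoxon rank-sum test.

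Pain is measured on the NRS (Variables and Measurement Instruments): "The NRS is an 11-point scale presented as a horizontal line", running from 0 to 10. The Data Collection section makes T1 the primary time point. The Sample Size section plans for a difference of 1.5 NRS points: "An estimated SD of 2.61 was selected based on a conservative approach", from reported SDs of 1.4 to 2.8.

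**The concern.** Pain is an outcome variable, and the conditional paragraph covers all outcome variables. A reader cannot tell whether the mixed model for pain is fixed or depends on the Lilliefors results. The article does not say how many of the six cells must pass, and it moves from considering nonparametric methods to performing one. The choice is therefore left to the data and to the analyst.

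The score takes only 11 integer values and is bounded at both ends. A test designed for continuous normal data can reject it because of ties and the floor, with nothing wrong in the comparison of means. At stake are the pre-specification of the primary method, an estimate in the units of the 1.5-point target, and the Cohen d that the plan promises.

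**Working it through.** **1. The plan's own figure.** Inputs from Sample Size: difference 1.5, SD 2.61, α 0.05 (two-sided assumed, since the side is not stated), power 80%, dropout 10%.

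n per arm = 2 × (1.960 + 0.842)² × 2.61² / 1.5² = 47.5, so 48. Inflated for dropout: 48 / 0.90 = 53.3, so 54 per arm and 108 in total. The stated 108 is reproduced. It is a calculation for a difference in means.

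**2. The gate with ideal data.** With exactly normal, continuous data and six independent tests at 5%, all six pass with probability 0.95⁶ = 73.5%. The rule would discard the model about one time in four even when its assumption is true.

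**3. One cell of integer scores.** Scores were simulated as a normal latent value, rounded and clipped to 0–10, with n = 54 and a simulated 5% Lilliefors critical value of 0.120. The SDs span the article's range. The means and the latent normal shape are assumptions. Chance that one cell is rejected:

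| Latent SD | Mean 2 | Mean 3 | Means 4–6 |
|---|---|---|---|
| 1.4 | 100% | 99.9% | 99.8–99.9% |
| 2.0 | 99.6% | 89.7% | 83.5–84.5% |
| 2.61 | 99.3% | 83.3% | 57.6–63.2% |
| 2.8 | 99.2% | 84.8% | 52.2–59.9% |

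A mid-scale cell at the planning SD therefore passes about 4 times in 10. Six independent cells at the most favourable of these rates for SD 2.61 give (1 − 0.576)⁶ = 0.6%.

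**4. Whole trials.** 49 per arm (54 × 0.9 = 48.6), baseline mean 5, within-person correlation 0.3 to 0.7, true difference 0 or 1.5 points:

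| Latent SD | All six cells pass | Both T1 cells pass |
|---|---|---|
| 1.4 | 0% | 0% |
| 2.0 | at most 0.05% | 3.9–5.3% |
| 2.61 | 0.6–2.0% | 16.7–24.5% |
| 2.8 | 1.1–2.8% | 18.3–29.5% |

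With 54 per arm and five other sets of visit means, all six passed in 0–1.2% of trials.

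**5. What the switch costs.** A t test on T1 change stands in for the mixed-model contrast, with complete data, 49 per arm, SD 2.61 and a difference of 1.5:

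| Correlation | t test on change | Rank-sum on change |
|---|---|---|
| 0.3 | 63.8% | 61.6% |
| 0.5 | 78.0% | 76.1% |
| 0.7 | 93.7% | 92.8% |

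Correlation 0.5 is the case closest to the sample-size calculation, because the SD of change is then 2.61 × √(2 × (1 − 0.5)) = 2.61. With no true difference, both tests rejected in about 5% of trials. At SD 2.61–2.8 and correlation 0.5, with a true difference of 1.5 points, the two tests fell on opposite sides of .05 in about 4–7% of trials. With no true difference the figure was about 2%.

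**The case against.** The strongest defence is that the sentence about pain is specific and unconditional, the paragraph about normality is general, and the fallback is at first only to be considered. On that reading the mixed model stands. This is a fair reading, and it is why a reader who infers that the primary analysis *will* be replaced by rank-sum goes further than the text. It does not remove the contradiction, because pain is nowhere exempted and the rank-sum sentence is firm.

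Nor do the documents support saying that the score almost never passes. No rule says that all six cells must pass, and one mid-scale cell at SD 2.61 passes about 40% of the time. The low figures belong to the joint tests.

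A reader might also object that the gate tests the wrong thing, raw scores rather than residuals. That is too strong here. With only group, time and their interaction as fixed effects, the model fits one mean per cell, so with complete data the marginal residuals are the scores minus their cell means. Cell normality is then close to marginal-residual normality. The narrower criticism stands: the pretest is unnecessary, because with about 50 women per arm the mean contrasts are robust to this degree of non-normality.

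Three further harms might be inferred and do not follow:

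- **Lost covariate adjustment.** The model lists no covariates.
- **Lost likelihood handling of dropouts.** The plan imputes missing data for all analyses.
- **New multiplicity from T1 and T2 tests.** T1 is already primary, and the mixed model yields both contrasts too.

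A Hodges–Lehmann shift with its interval could accompany rank-sum in NRS points. The plan does not name it, and it is not the mean difference used for sample size.

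**Conclusion.** Wrong as written, and to be corrected before analysis, but not a threat to the trial's validity. The article gives two incompatible statements of the primary analysis of pain. This is a stated rule that conflicts with another, not detail left to a fuller plan.

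If the conditional statement is followed, the mixed model would be retained in about 0–3% of simulated trials when all six cells must pass, and in about 0–30% when only the T1 cells count. These ranges rest on the article's SD range and on assumed means, correlations and a rounded-normal shape.

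The main loss is the pre-specified mean difference on the 1.5-point scale and the model-based Cohen d. The choice of test could also occasionally decide significance. The power cost is about 2 percentage points, type I error is essentially unchanged, and the sample size of 108 stands.

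**What to change.** Amend the Data Analysis section to say:

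- The linear mixed model is the primary analysis of pain, regardless of the result of any normality test.
- The primary estimate is the group-by-time contrast at T1, that is, the between-group difference in change from baseline, in NRS points with its 95% CI. Cohen d is derived from this contrast.
- The normality gate is removed for the other continuous outcomes as well.
- Residual checks are reported. A bootstrap or robust-standard-error CI for the T1 contrast and the rank-sum test on change are named sensitivity analyses, and they do not replace the primary result.

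The cost is a few sentences. No data collection or sample size changes. The Results section reports about 80 women recruited and no data analysis begun, so a dated change made now cannot be driven by the results.

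### The planned T1 pain effect is an unadjusted difference in change from baseline: unbiased, but less precise than a baseline-adjusted estimate, and its power depends on a pre-post correlation the protocol does not give

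*Protocol article*

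**What the plan says.** Under Data Analysis, the inferential analyses are described as "between-group comparisons (intervention vs control) based on pretest-posttest change scores". The primary analysis of pain compares changes from baseline between the arms in a linear mixed-effects model with a random intercept per participant. Its terms are given as follows: "The models will include fixed effects for group (control vs intervention), time (baseline, T1, and T2", and the list closes with the group-by-time interaction. Baseline is thus one level of the outcome, and the groups may differ freely there. Cohen d is to come from differences described as adjusted, but no baseline value or other covariate is listed. Outcomes that fail the normality check go to a Wilcoxon rank-sum test, again on change scores. Data Collection names T1 (6 weeks) as the primary time point.

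Under Sample Size, the trial is sized for a "minimum detectable difference of 1.5 points in pain intensity measured using the numerical rating scale (NRS" scale, with 80% power and a type I error of 0.05. On variability it says: "An estimated SD of 2.61 was selected based on a conservative approach considering the variability reported in breast cancer populations using the NRS", and of the source studies, "where SDs range from 1.4 to 2.8". Neither a pre-post correlation nor an SD of change is given.

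**The concern.** Two things do not fit together well.

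First, the estimator subtracts the whole of a single-item baseline pain score. Where that score correlates only moderately with the T1 score, full subtraction adds noise. Regressing on baseline removes only the part that predicts the outcome. The T0 score is collected in any case, so the precision is given up for nothing. The Randomization section also plans simple randomisation and names no stratification, so some chance imbalance in baseline pain is possible. A change score tends to over-correct such an imbalance, through regression to the mean.

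Second, the sample size formula compares two independent means and uses what reads as the SD of a score, while the planned contrast is a difference in change. The two SDs coincide only when r = 0.5. At lower r, the planned analysis has less power than the one for which the trial was sized.

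**Working it through.** **Inputs.** From Sample Size: difference 1.5, SD 2.61, power 80%, type I error 0.05, dropout 10%. From Randomization: 1:1 allocation. Assumed: a two-sided test (the article does not say for the primary test, but two-sided reproduces its total and one-sided gives 86); 2.61 is the SD of one NRS score; equal variances at T0 and T1; a range of r.

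**Step 1: reproduce the stated figure.** n per arm = 2 × [2.61 × (1.960 + 0.842) / 1.5]² = 47.5, rounded up to 48. Then 48 / 0.90 = 53.3, rounded up to 54 per arm, or 108 in total. This matches the article. The formula contains no correlation.

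**Step 2: what the planned model estimates.** With baseline as an outcome level and group and group-by-time both free, the T1 interaction with complete data is the difference in mean change. Fitting the model to two simulated complete data sets gave -0.7116 and -1.5948, identical to the raw differences in mean change.

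**Step 3: the two SDs.**
- Change score: 2.61 × √(2(1 − r)).
- Baseline-adjusted: 2.61 × √(1 − r²).
- Variance ratio, adjusted to change: (1 − r²) / (2(1 − r)) = (1 + r)/2, which is below 1 for every r below 1.
- With unequal SDs s0 and s1, change-score variance minus adjusted variance is s0² + s1² − 2r·s0·s1 − s1²(1 − r²) = (s0 − r·s1)². This is never negative, so adjustment does not lose precision in large samples.

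**Step 4: power** (two-sample t, 48 per arm, difference 1.5).

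| r | SD of change | Power, change | SD adjusted | Power, adjusted |
|---|---|---|---|---|
| 0.3 | 3.09 | 65.4% | 2.49 | 83.2% |
| 0.4 | 2.86 | 72.0% | 2.39 | 86.0% |
| 0.5 | 2.61 | 79.6% | 2.26 | 89.6% |
| 0.7 | 2.02 | 94.9% | 1.86 | 97.4% |

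Total N for 80% power after dropout (normal approximation), change against adjusted: 150 against 98 at r = 0.3; 130 against 90 at 0.4; 108 against 80 at 0.5.

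**Step 5: where the change score reaches 80%, and how far that point moves.** With 48 per arm (normal approximation), the SD of change may be at most 1.5 × √24 / 2.802 = 2.62. Hence r must be at least 1 − 6.88/(2·SD²), where SD is that of a single score:
- SD 2.8 (top of the article's range): r ≥ 0.56.
- SD 2.61: r ≥ 0.50 (0.495; 0.505 by the t test).
- SD 2.1 (middle of the range): r ≥ 0.22.
- SD 2.0: r ≥ 0.14.
- SD about 1.85 or less: any r ≥ 0 is enough.

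If all 54 per arm gave full information at SD 2.61, the threshold would be 0.43 to 0.44. If 2.61 were already an SD of change, power would be about 80% whatever r is.

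**The case against.** The strongest reply is that this is not an error. A difference in change is unbiased under randomisation, its type I error is valid, and a group-by-time mixed model is a standard longitudinal analysis. That stands: the point concerns efficiency and the match between analysis and sample size.

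A reader might infer that the trial is underpowered, or that 80% power requires r of 0.5 as a matter of fact. The documents support neither. The article gives no r. The 0.5 threshold needs 2.61 to be the true SD of a single score, equal variances at both times, and 48 evaluable per arm. The article calls 2.61 conservative, and over much of its own SD range the threshold is well below 0.5. The score reading of 2.61 is the natural one but remains an inference. With no minimum pain score for entry, floor effects could also make the variances unequal, so the powers above are guides.

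A reader might also infer that no adjustment will be made. The article says only which terms the models will include, and a fuller plan may add covariates. The fair statement is that none is listed, although the text calls the differences adjusted.

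One further objection stands and shapes the remedy. If pain fails the normality check, the plan moves to a rank-sum test on change scores, and a change to the mixed model alone would never apply. The powers above do not cover that test.

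**Conclusion.** The concern holds as a matter of precision. As listed, the T1 pain contrast is a difference in change and is less precise than a baseline-adjusted one: with equal variances, the adjusted estimate has 65% of its variance at r = 0.3, 75% at 0.5 and 85% at 0.7.

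The power consequence is conditional. At SD 2.61 with 48 evaluable per arm, the planned contrast reaches the stated 80% only from r of about 0.5 upward. Baseline adjustment gives about 80% or more at any r from 0 upward. The article offers no basis for assuming r that high, nor any evidence that it is lower. The plan should be changed because adjustment removes the dependence on r, not because a shortfall has been demonstrated.

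**What to change.** For pain and the other continuous outcomes, model T1 and T2 as the outcomes, with that outcome's own T0 value, T0-by-time, group, time and group-by-time as fixed effects. Alternatively, keep T0 as an outcome and constrain the two groups to a common baseline mean. The two need not agree exactly under a random-intercept covariance, so name one in advance. Report the adjusted T1 mean difference with its 95% CI, and base Cohen d on it.

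State that this model remains the primary analysis of pain even if the Lilliefors check fails, with the rank-sum test on change scores as a sensitivity analysis only. In Sample Size, say whether 2.61 is an SD of scores or of change.

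The cost is a few lines of text and one altered model statement in SPSS. No new data are needed, since T0 values are already collected. The article reports about 80 women recruited and no analysis begun, so the change can be dated and recorded before any outcome comparison is seen.
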